### Methods in analysis to handle protocol non-adherence and any statistical methods to handle missing data {20c}

The missing at random assumption for primary outcome data will be assessed further in sensitivity analyses. Treatment effects will be estimated under varying assumptions of data being missing not at random using pattern-mixture models. A complete case analysis will also be conducted.

### Plans to give access to the full protocol, participant-level data and statistical code {31c}

Access to the full protocol, participant-level data and statistical code will be available from the OSF.

### Oversight and monitoring

#### Composition of the coordinating centre and Trial Steering Committee {5d}

[name] from The Centre for Mental Health (CMH) has oversight of the project management on behalf of the funders. The Chief Investigator [CI] ([name]) has overall responsibility for the research.

A Research Management Group (RMG), which the CI will chair, comprising all authors, will advise and assist on the project’s management. The RMG meets every 6 weeks.

An Expert Reference Group (ERG), a group of independent research experts and lay people and the CI, will provide subject matter expertise to the funders and work with the CMH and London South Bank University’s representatives to guide and oversee the impact of the research. The ERG meets quarterly for the entirety of the project’s duration.

#### Composition of the data monitoring committee, its role and reporting structure {21a}

Data monitoring will be conducted by the Trial Steering Committee (TSC) comprising a trialist, statistician and health economist and will act as Data Safety Monitoring Board (DSMB). The TSC will oversee the conduct of the trial independently of and on behalf of the project funders and sponsors and ensure it is carried out with reference to good practice. The TSC will have ultimate responsibility for deciding if the trial should be stopped on grounds of efficacy. The TSC is a sub-group of the project Expert Reference Group (ERG) set up by the funders and will audit the trial conduct through reports submitted to it by the researchers on a three-monthly basis.

#### Adverse event reporting and harms {22}

We anticipate little risk to participants in the study. The Senior Manager in each company will be asked to report to the CI in writing any adverse or untoward incidents that occur because of the study. The CI will assess each adverse event and decide on an appropriate course of action. In case of serious adverse events (SAEs), i.e. those causing serious injury or death, the CI will notify the Ethics Committee and the TSC as soon as possible after being notified. A TSC within the ERG consisting of members independent of the investigators, their employing organisations, funders and sponsor will monitor trial progress and conduct and will have ultimate responsibility for deciding if the trial should be stopped on the grounds of safety.

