## Introduction

### Background and rationale {6a}

Mental Health First Aid (MHFA) is a mental health intervention on how to identify, understand and help someone who may be experiencing a mental health issue. It is designed to help Mental Health First-Aiders to listen, reassure and respond, even in a crisis—and potentially stop a crisis from happening. MHFA courses were developed in 2000 to equip trainees with first-aid skills to support people with mental health problems [1]. MHFA training is reported to increase trainees’ knowledge, confidence and skills in identifying mental health problems, as well as reducing negative attitudes and stigma [1–4].

Reviews of the implementation of MHFA found between 68 and 88% of trained mental health first aiders had used their skills when in contact with someone experiencing mental health difficulties [5–7]. Mental health interventions in the workplace have been linked to increased productivity, reduced levels of absenteeism and significant economic gains [8].

Recently, a large study (MENTOR) [9] investigated the implementation, use and utility of MHFA in the workplace using multiple research methods and reported that MHFA was useful for raising awareness of mental health in the workplace, but stated it may not be the best or only means of doing so and may not necessarily be the most cost-effective. The MENTOR study highlighted implementation issues relating to lack of clarity around the role of the mental health first aider and potential safety concerns, leading them to recommend further research and evaluation of the intervention. Implementation challenges such as role conflict relating to a person carrying out the first aider role versus other roles and responsibilities they may have within the organisation have been identified previously [10]. Handling the potentially hierarchical relationship between the mental health first aider and recipient, who may be a subordinate, is one such example of this potential role conflict [10].

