### Assignment of interventions: blinding

#### Who will be blinded {17a}

Participants, mental health first aiders and researchers will not be blinded to treatment allocation due to the nature of the study. However, independent staff helping to process the data, the trial statistician and health economist will all be blinded to intervention status.

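### The one stated adverse event route makes a manager judge causality before anything is recorded, so reported counts will tend to be too low and cannot validly be compared between arms

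*Protocol article*

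**What the plan says.** All from the protocol article.

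- **Adverse event reporting and harms {22}.** The reporter and the scope are fixed in one sentence: "The Senior Manager in each company will be asked to report to the CI in writing any adverse or untoward incidents that occur because of". Its scope is limited to "any adverse or untoward incidents that occur because of the study".
- **Same section, next steps.** "The CI will assess each adverse event and decide on an appropriate course of action". For serious events (defined as those causing serious injury or death), "the CI will notify the Ethics Committee and the TSC as soon as possible after being notified".
- **Criteria for discontinuing {11b} and data monitoring {21a}.** Serious adverse events may be grounds for stopping. The TSC acts as the safety board and works from reports that the researchers send every three months.
- **Who will be blinded {17a}.** "Participants, mental health first aiders and researchers will not be blinded to treatment allocation". Those listed as blinded are data-processing staff, the trial statistician and the health economist. Senior Managers are not on that list.
- **Choice of comparators {6b}.** Control organisations receive a brief consultation.
- **Background and rationale {6a}.** An earlier workplace study is cited for "implementation issues relating to lack of clarity around the role of the mental health first aider and potential safety concerns", and a further challenge is noted: "Handling the potentially hierarchical relationship between the mental health first aider and recipient, who may be a subordinate".
- **Table 1.** Employees report wellbeing, quality of life and service use at baseline, up to 3 months, and 6, 12 and 24 months. These are secondary or economic measures and are not described as harms data.

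**The concern.** The rule puts two filters ahead of the record. The manager must hear of the event, and must then believe that the study caused it. Both filters can only remove events. The second is a causality judgement made by a lay person before the Chief Investigator sees anything, so an event wrongly judged unrelated cannot be reviewed later.

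The second filter need not act equally in the two arms. A manager in an organisation that has trained and publicised first aiders has something to which an incident can be attributed. A manager whose organisation had only a brief consultation has very little. With allocation open, equal true risks can produce unequal counts.

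At stake are the adverse event information that reaches the TSC and any later statement about the safety of MHFA. The protocol's own background cites potential safety concerns among the findings that led to a call for further evaluation.

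**Working it through.** **Step 1. Follow an event through the stated route.**

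1. An incident happens to an employee.
2. The Senior Manager hears of it, or does not.
3. The manager judges that it occurred because of the study, or does not.
4. Only then is it reported in writing to the Chief Investigator, who assesses it.
5. If it is serious, the Chief Investigator notifies the Ethics Committee and the TSC.
6. The TSC otherwise relies on the researchers' three-monthly reports.

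Steps 4 to 6 see only what passed steps 2 and 3. No section of the article describes scheduled collection of events whatever their cause.

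**Step 2. Direction, which needs no assumed numbers.** Let *p* be the true risk, *h* the chance that the manager hears of an event, and *a* the chance that an event heard of is attributed to the study. Then

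expected reports per arm = *n* × *p* × *h* × *a*.

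Since *h* and *a* are at most 1, expected reports cannot exceed the expected number of true events. If *p* and *h* are the same in both arms, the apparent rate ratio is *a*(MHFA) / *a*(control). It equals the true ratio of 1 only if attribution is the same in both arms.

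**Step 3. Illustration.** The only input from the document is *n* = 400 per arm (Sample size {14}). The values of *p*, *h* and *a* are assumptions.

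Take *p* = 5% in both arms and *h* = 30%, with *a* = 50% in the MHFA arm and 10% in the control arm:

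| | MHFA | Control |
|---|---|---|
| True events expected | 400 × 0.05 = 20 | 400 × 0.05 = 20 |
| Reports expected | 20 × 0.30 × 0.50 = 3.0 | 20 × 0.30 × 0.10 = 0.6 |
| Share missed | 1 − 3.0/20 = 85% | 1 − 0.6/20 = 97% |

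The apparent rate ratio is 0.50/0.10 = 5 when the true ratio is 1. If events are treated as independent, the chance that the control arm reports nothing at all is (1 − 0.05 × 0.30 × 0.10)^400 = 0.55, despite 20 expected events.

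The range examined was *p* from 2% to 10%, *h* from 10% to 50%, and attribution of 50% v 50%, 50% v 10% or 20% v 2%:

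- true events expected per arm: 8 to 40;
- reports expected: 0.16 to 10 (MHFA) and 0.02 to 10 (control);
- apparent rate ratio: 1 to 10.

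**Step 4. What a count of zero would mean.** With full ascertainment, zero events among 400 gives a 95% upper limit of 1 − 0.05^(1/400) = 0.75%. If only a fraction *d* of events is both heard of and attributed, the limit on the true risk is 0.75%/*d*: 1.5% at *d* = 50%, 2.5% at 30% and 7.5% at 10% (assumed values).

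These calculations ignore clustering, although reports would come through 12 managers per arm. They also take all 400 as the denominator, although the Primary outcome section describes those who receive MHFA as a small non-random subsample.

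**The case against.** The best case for the plan is proportionality. The protocol anticipates little risk, the intervention is workplace training, and a light reporting system is defensible. Stopping is tied to serious events, which are the ones an employer is most likely to learn of, so very low ascertainment is least plausible there. This has weight for the hearing filter. It does not answer the attribution filter, which applies to serious events too.

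Three stronger readings are tempting, and the document does not support them.

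- **That employees and first aiders have no way to report harm.** The article states none. But it condenses a longer protocol, and every employee receives an information sheet covering potential harm and study procedures. Neither is shown, and either may give a contact. An optional contact would still not be systematic collection in both arms, and would not remove the causal condition.
- **That the arms cannot be compared on safety at all.** Self-reported wellbeing, quality of life and service use are collected in both arms without passing through the manager. They remain comparable and could show average deterioration, but they do not identify individual events. Nor does the article plan a between-arm comparison of adverse events or a declaration that MHFA is safe. The point is that the reported counts could not support either.
- **That the background section establishes specific harms the manager would miss.** It mentions potential safety concerns without describing them. Role conflict and hierarchy are presented as implementation challenges. That a subordinate might not tell a manager is a reasonable inference, but the protocol does not say it.

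The illustrative figures are also open to challenge, since every rate in them is assumed. They show how the rule behaves, not what will happen in this trial.

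**Conclusion.** The point holds for the causal condition on reporting, which the article itself fixes. Counts obtained by this route will tend to be too low and may be too low by different amounts in the two arms. They are not a valid basis for comparing arms or for a statement about safety.

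The direction of the under-count follows from the rule alone. The difference between arms arises only if attribution differs by arm, which is plausible given open allocation and a control condition of one brief consultation. The size of either cannot be computed from the document. Over the assumed range, the apparent rate ratio runs from 1 to 10 when the true ratio is 1.

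The sample size and the primary efficacy analysis are untouched. This is an improvement worth making because it is cheap, not a flaw that undermines the main result.

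**What to change.** 1. In Adverse event reporting and harms {22}, remove the condition that the incident occurred because of the study. Ask for adverse incidents among participants known to the organisation, in both arms, whatever the presumed cause. Judge relatedness afterwards, blinded to arm where possible.
2. Add one short harms item to the existing surveys at up to 3, 6, 12 and 24 months. Word it identically in both arms and do not tie it to MHFA or to workplace support, since that would bring an attribution filter back. Ask about any perceived link in a separate question.
3. State a direct reporting route to the research team, if the full protocol or information sheet does not already give one.
4. Tabulate events by randomised arm for the TSC.

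**Cost.** One or two survey items, an ethics amendment, more non-specific events to review, and a procedure for handling disclosures of distress. Survey coverage is limited to responders. With the protocol's 40% response and 15% attrition at 6 months, that is about 0.40 × 0.85 = 34% of employees, so the survey item adds to organisational reporting and does not replace it.

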#### Intervention description {11a}

The MHFA intervention has three parts:
The 2-day MHFA training provided by MHFAE. This is a manualised training programme designed to provide individuals with the following: an in-depth understanding of mental health and the factors that can affect wellbeing, practical skills to spot the triggers and signs of mental health issues, confidence to step in, reassure and support a person in distress, enhanced interpersonal skills such as non-judgemental listening, knowledge to help someone recover their health by guiding them to further support—whether that is self-help resources, through their employer, the NHS, or a combination.Raising awareness of the presence of MHFA in the organisation.The application of MHFA to participants in the workplace. The MHFA training uses a manualised five-stage approach, ALGEE: Approach the person, assess and assist with any crisis; Listen and communicate non-judgementally; Give support and information; Encourage the person to get appropriate professional help and Encourage them to seek other forms of support.

MHFAE recommend training one employee in MHFA per ten employees; however, organisations are free to ask for any number of employees to be trained. The current study will record the ratio of participants trained in each organisation. No stipulation is made as to the selection of participants to be trained, and organisations are encouraged to advertise the training to all staff. The selection criteria used by each organisation will be assessed in the qualitative component of this study.

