#### Criteria for discontinuing or modifying allocated interventions {11b}

A Trial Steering Committee (TSC), which will audit the conduct of the study, will have ultimate responsibility for deciding if the trial should be stopped on grounds of safety or efficacy. The occurrence of serious adverse events to participants will be assessed by the TSC and may be grounds for discontinuing the trial.

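### The stated SAE definition covers only serious injury or death, so serious psychiatric events without such injury have no required route to the committee that decides on safety

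*Protocol article*

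**What the plan says.** Section {22} of the protocol article sets out the reporting chain. The Senior Manager of each organisation is asked to report to the CI, in writing, "any adverse or untoward incidents that occur because of the study". Next, "The CI will assess each adverse event and decide on an appropriate course of action". One class of event has a prescribed onward route: "In case of serious adverse events (SAEs), i.e. those causing serious injury or death, the CI will notify the Ethics Committee and the TSC", and this is to happen promptly. The same section says of the TSC that it "will have ultimate responsibility for deciding if the trial should be stopped on the grounds of safety".

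Two other sections bear on the TSC's role. Section {11b}, on discontinuing interventions, states: "The occurrence of serious adverse events to participants will be assessed by the TSC and may be grounds for discontinuing the trial". Section {21a}, on data monitoring, makes the TSC the trial's data and safety monitoring board and says that it "will audit the trial conduct through reports submitted to it by the researchers on a three-monthly basis". It does not say what safety content those reports have.

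On the intervention itself, section {11a} describes a five-stage approach that begins: "Approach the person, assess and assist with any crisis".

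**The concern.** MHFA asks trained colleagues to approach people in distress, and to help in a crisis. The serious harms one would foresee are mainly psychiatric: a suicidal crisis that is handled badly, self-harm with little physical damage, or an admission to psychiatric care. The background section itself reports that an earlier large workplace study of MHFA found the first-aider role unclear and raised possible safety concerns.

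The SAE definition is framed around injury and death, so it fits these harms poorly. It also determines what must be sent to the TSC. A safety committee can recognise a pattern across organisations only if it sees the events together. If several crises occurred in different MHFA organisations, each could be dealt with singly by the CI, who carries overall responsibility for the research. No stated duty would require the accumulation to be shown to the independent body charged with the safety decision.

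**Working it through.** No arithmetic applies. The point rests on the wording of four sections, taken in order.

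1. **Is the definition closed?** In {22} the term SAE is followed by an equating phrase (i.e.), not by examples. As written, SAEs are the events that cause serious injury or death and no others. Life-threatening events without injury and hospital admission are not named.

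2. **Which events must reach the TSC?** Only SAEs have a stated mandatory notification ({22}). Section {11b} ties the TSC's assessment, and possible discontinuation of the trial, to the same term. The definition therefore sets the minimum that the TSC must be told.

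3. **What happens to other events?** {22} has the CI assess each one and choose what to do. Forwarding to the TSC is neither required nor excluded.

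4. **Is there a second route?** {21a} provides three-monthly reports from the researchers. Their stated purpose is to audit trial conduct. Adverse events are neither included nor excluded.

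5. **Sorting the foreseeable events by these rules:**
   - A crisis ending in death or serious injury, once reported to the CI, is an SAE and must be notified to the TSC.
   - A psychiatric admission, or a suicidal or self-harm crisis without serious injury, once reported to the CI, is on an ordinary reading not an SAE. The CI decides, and no onward report is required.
   - A crisis that the Senior Manager does not attribute to the study is not requested from the manager, so it may not reach the CI at all.

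6. **Does this match the intervention?** Crisis help is the first of the five stages in {11a}. The second group in step 5 is therefore directly relevant to this intervention, and it is the group without a required route.

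Sections {11b} and {22} agree with each other: SAEs go to the TSC, and the TSC decides on stopping for safety. The fault is the narrowness of a stated rule, not a contradiction.

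**The case against.** A reader might infer something stronger: that every event short of serious injury or death ends with the CI, and that the TSC never sees a mental health crisis. The article does not support that. The course of action left to the CI can include escalation. Nor does the article say that the CI acts alone, since a management group advises on running the project. The SAE sentence sets a prompt notification route and does not say that it is the TSC's only source of information. The TSC acts as the safety monitoring board and receives regular reports, and a crisis that ends in serious injury or death does qualify. All of this stands, and it limits the point to what is required.

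A second objection is that this is a condensed article, and that a full protocol or committee charter would normally specify the contents of the TSC reports. That is fair as far as the reports go, and their unstated content is not itself a fault. It does not answer the definition, which the article states outright. A fuller document would have to depart from that wording to make psychiatric crises SAEs.

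Third, serious injury is not expressly limited to bodily injury, so a generous reader could include severe psychological harm. That is possible, but a manager or investigator applying the phrase in its ordinary sense would be unlikely to count an admission or an averted suicide attempt. The ambiguity is itself a reason to spell the definition out.

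Fourth, the trial expects little risk to participants, and the upstream filter means that some crises would be missed whatever the SAE definition says. Both points stand. They make the matter modest, and the second limits what the fix can achieve.

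**Conclusion.** The point holds in a limited form. The article defines SAEs too narrowly for an intervention that includes crisis help, and the definition governs the only notification to the TSC that is mandatory. Serious psychiatric events without serious injury are left to the CI's discretion. They may reach the TSC by escalation or through the three-monthly reports, but nothing stated makes them do so.

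No number can be put on the gap. The article gives no rate for such events, and any count would also depend on which incidents managers attribute to the study. The conclusion rests on an ordinary reading of serious injury, and on the article's definition being the one in force in the full protocol. It is a worthwhile, inexpensive improvement to safety oversight. It does not show that the TSC would be kept uninformed.

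**What to change.** Make two changes of wording.

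- In {22}, widen the SAE definition beyond serious injury and death to cover life-threatening events, hospital admission, and serious psychiatric events such as a suicidal or self-harm crisis. Section {11b} uses the same term and then needs no change.
- In {21a}, state that the three-monthly TSC reports include a cumulative list, by arm, of all adverse events reported to the CI, including those judged non-serious. The researchers who write these reports are not blinded ({17a}), so they can prepare the list without unblinding the trial statistician.

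The cost is a few lines of text and one table in a report that already exists. The downside is more notifications, some for events unrelated to MHFA.

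The limit should be stated alongside the change. The list will contain only what Senior Managers report, and they are asked only for incidents that they attribute to the study. It will describe reported events, not the frequency of crises in either arm.
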